**Figure 3 figure3:**
[figure not shown]
Study site and school locations. Map generated through ArcGIS program (ESRI Inc, Redlands, CA, USA).

### Recruitment of Study Participants

Study participants were Grade 4 students (aged 9-10 years) from the selected schools. To ensure that all parents were engaged and informed about the study, the research team, with the assistance of the village or barangay health workers (BHWs), organized parents and caregivers’ meetings at the catchment barangays of the schools included in the MGP trial before the commencement of classes in June 2016. The BHWs who assisted in the parents/caregiver’s meeting were oriented by the research staff on STH and the MGP study. The STH orientation aimed to empower the BHWs about intestinal worms and relate these with preventive measures in other DOH programs, such as sanitation and hygiene. The orientation about the MGP study provided the BHWs with the information necessary to invite and ask the parents or caregivers to attend the meetings. The research staff were responsible for obtaining parental informed consent after the parents and caregivers’ meeting. Caregivers who were not reached through the caregiver’s meetings were located and oriented by the BHWs in their homes; the research staff validated the information provided to these parents and caregivers during home visits and obtained written consent.

One week before the baseline survey, the Grade 4 students in both the intervention and control schools were oriented about the study and the different study procedures to be conducted on them. However, information regarding cartoon viewing was provided only in the intervention schools. An informed consent document was also distributed to the students whose parents were not present during the parents and caregivers’ meeting in the barangay. These students were asked to return the signed informed consent form to the research staff on the day of the survey. The inclusion criteria for schoolchildren were as follows: (1) enrolled in Grade 4 and (2) had parental informed consent.

### Data Collection

#### Field Organization, Training, and Field Schedule

Four teams were set up and organized to carry out the data collection procedures in the 40 participating schools before the commencement of the National Deworming Month. Each team, composed of 1 supervisor from the Department of Epidemiology and Biostatistics from the RITM in the Philippines, 1 team leader, and 6 medical technologists, was responsible for collecting data from 2 to 3 schools per week.

Before the start of the survey, the research staff had undergone a 2-week training. The first week was a microscopy proficiency training conducted by the National Reference Laboratory for Parasitology of RITM, whereas the second week focused on data collection procedures, filling out of forms, and administration of the data collection tools.

Four visits were made at each school at baseline and during the 2 follow-up surveys to allow the children with multiple opportunities to participate in all the data collection procedures, if they were absent during previous visits. On the fifth day, a review of the data collection forms was done to ensure accuracy, consistency, and completeness of the information collected before the departure of each team from the schools and moving to the next set of schools.

#### Stool Surveys

Stool samples were collected at baseline and at 2 follow-up surveys. A week before the survey week, the participating children, following their orientation to the study, were requested to provide 2 stool samples as part of their involvement in the project. Each child was given a stool collection kit that included a stool container, gloves, an applicator stick, and instructions on how to collect a stool sample. Children were instructed to collect 2 stool samples on any morning of the 4 collection days. They were asked to submit only 1 sample per day (normally in the morning of the same day of collection) to the research staff in the school. The samples were collected, processed at the school site within 2 hours after collection, and read the same day using 3 KK thick smears (41.7 mg of stool/smear) prepared per sample [47]. A team of trained microscopists read the slides. The microscopists worked independently of each other on the samples assigned to them, with 1 sample examined by 1 microscopist only. The number of STH eggs was counted and recorded separately for each helminth species. To ensure the validity and accuracy of the results, 10% of all slides were randomly selected and reexamined by a reference microscopist on each collection day.

#### Knowledge, Attitude, and Practices Survey

All study participants were administered a questionnaire on STH-related KAP at baseline and at the 2 follow-up surveys. The KAP questionnaire consisted of multiple-choice and open-ended questions regarding demographics, health characteristics, medical history, and previous health education; knowledge about intestinal worms, how they are transmitted, and the symptoms and treatment of STH infection; the student’s attitude toward STH; self-reported hygiene practices with respect to hand washing, handling of food, using the toilet, and wearing of shoes; and household characteristics relating to household water source and household assets. The questionnaire was translated into Tagalog and back-translated to English to ensure accuracy. It was piloted in March 2015 in 2 schools outside the main trial area on a total of 83 schoolchildren from San Andres ES in the municipality of Alaminos (n=26) and Gulod ES in the municipality of Calauan (n=57).

Two research staff members were responsible for administering the questionnaire. One gave instructions to the children and read the questions one-by-one in front of the class, whereas the other moved around the room to check whether the children were able to follow the instructions and to ensure that each question was answered.

Students were considered to have a positive (or correct) attitude toward STH if they were aware of the risk of infection and intended to change their behavior to prevent an infection. Students were considered to have a negative (wrong) attitude if they did not recognize the health risk of STH and the importance of correct behavior (eg, good hygiene). A higher score in the questionnaire was considered indicative of a more positive attitude.

#### Anthropometric and Hemoglobin Measurements

Using a height scale chart (paper beam chart) and calibrated digital weighing scale (Tanita HD-383, Tanita Corporation, Japan), all participating children underwent measurement of height (to nearest 0.1 cm) and weight (to nearest 0.1 kg), respectively, obtained as a single measurement at baseline and at the 2 follow-up surveys. Fingerprick blood samples for hemoglobin measurement (using a portable hemoglobin analyzer [HemoCue Hb 301 System, HemoCue Sweden]) were also collected from 2000 randomly selected children with matching data on the KAP and at least one stool sample at baseline and at the 2 follow-up surveys. Using the height and weight measurements collected from the children, anthropometric values indicative of their nutritional status were calculated. Indicators for malnutrition included stunting (height-for-age), thinness (BMI-for-age), and being underweight (weight-for-age). These anthropometric indicators were calculated as Z scores (the number of SDs from the mean of the standard population, with malnutrition and severe malnutrition defined as values 2 and 3 SDs, respectively, below the mean score of the standard population [48,49]), employing the 2007 WHO growth standards for SAC and adolescents [49]. Anemia was defined according to the WHO classification guidelines, adjusted for altitude in communities more than 1000 m above sea level [50].

#### Collection of Attendance and Academic Performance

The attendance for the school year and academic performance based on grades or end-of-quarter marks in English and mathematics for each of the 4 grading periods of the participating children while they were in Grades 3, 4, and 5 were accessed from the school records and were obtained in September 2016, March 2017, and November 2018, respectively. The end-of-school-term marks were defined as the arithmetic mean of the 4 grading periods in each school year. The attendance rate was defined as the number of days the children had attended school over the total number of days in 1 school year.

#### Treatment

Upon completion of each survey (ie, baseline and first and second follow-up), parasitological and hemoglobin results were communicated to all parents in an enclosed envelope, with a recommendation for treatment (if necessary) at the local health center or a request to participate in the deworming activity at school. All participating children were encouraged to take the deworming drug (albendazole [400 mg], as recommended by the WHO) provided free of charge. The school principal, teachers, and/or assisting health professionals (nurses) at each school monitored the students for treatment compliance. In collaboration with the school principals and teachers, the research staff collected the data on the deworming status of the participating students, any side effects experienced, and the reason why any student failed to take the drug.

#### School Facility Survey

In 2015, before the main trial, a school facility survey was conducted, whereby Grade 4 classrooms in all 40 schools included in the MGP trial were visited and assessed for the presence of toilets, water facilities, and hand washing area, and their functionality.

#### Household Survey

A household survey was conducted by trained interviewers on a subset of randomly selected students (n=400; households of 10 schoolchildren from each of the 40 participating schools) between October 23 and November 22, 2017, to assess the household support and facilities that promoted STH preventive behavior among the participating schoolchildren. Informed consent was obtained from each student’s parent or caregiver, and a structured interview was administered to them. The structured interview covered questions related to knowledge on STH and health education, household assets, and household infrastructure related to WASH. Rapid assessments of the hand-washing facilities and toilets available in the selected households were also conducted.

### Data Quality Assurance and Processing

#### Quality Assurance of the Field Data Collection

Field data quality was monitored through quality assurance by research investigators. All questionnaires and data collection forms were reviewed for accuracy, consistency, and completeness. This review was undertaken immediately after data collection, before the respective research teams had left the area.

#### Management and Processing of Qualitative Data

All qualitative FGDs and interviews were conducted in English and Tagalog. Informed consent was obtained from all study participants (teachers and from the parents of children involved). All FGDs and interviews were audio recorded, transcribed verbatim, coded, and analyzed.

### Data Management and Confidentiality

All results collected from the study respondents were kept confidential. Stool samples were labeled using each participant’s assigned study ID number, with no identifying information. Reports that had been generated from this study only contained a summary of the data collection without the names of the respondents.

Results of parasitological assessments, KAP surveys, school attendance information, academic performance, deworming data, height, weight, and hemoglobin measurements were entered twice by 2 different data encoders in a customized password-protected data entry system developed using Microsoft Access [51]. The data entry system contained validation codes and built-in range checks for appropriate variables. The final study datasets were accessible only to the study investigators. All study forms were placed in a locked cabinet in a study office at RITM.

### Study End Point Analyses

Models for infection will use generalized estimating equations (GEEs), and a logistic regression model will be used to estimate odds ratio and, therefore, intervention efficacy against infection, accounting for clustering within schools, repeated measures, and baseline infection. Stratification by school-based baseline prevalence will be undertaken to evaluate intervention efficacy at low and high endemicity. Analyses of changes in knowledge and self-reported behavior scores will be analyzed with the use of a linear regression model and GEE to take into account clustering within schools and repeated measures. Potential confounders such as age, sex, and rural or urban status of schools will be incorporated. Spearman correlation coefficients will be used to estimate correlations among self-reported behavior, knowledge, and incidence.

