### Study Setting

Approximately 43 million children are at risk of STH infection in the Philippines (2016 figures, calculated using the Preventive Chemotherapy Databank, maintained by the WHO); of these, about 24% are pre-SAC, whereas 76% are SAC [32]. The burden caused by STH infections remains high according to the results of several studies conducted in the country. A nationwide survey performed in 2001 and reported in 2005 found that the STH prevalence among schoolchildren was as high as 67% [33]. A subsequent study in 2006 showed a prevalence of 54% for at least one type of STH infection and a prevalence of 23.1% for heavy-intensity infections [34]. In a follow-up survey in 2009, a decrease in the overall prevalence (44.7%) and heavy-intensity STH infections (19.7%) among SAC (aged 6-12 years) was reported [35]. Although the prevalence had decreased, it still exceeded the 20% target for morbidity control set forth by the WHO.

The current Philippines national control program for STHs involves semiannual MDA for schoolchildren aged 6-12 years in all public elementary schools (ESs), as advocated by the WHO. This has been implemented since 2007 by the DepEd in collaboration with the DOH through its Integrated Helminth Control Program (IHCP) [36]. As part of the long-term strategy, the IHCP also incorporates health education/promotion and WASH interventions through the DepEd [37,38]. However, the persistently high prevalence of STH reported across the country suggests that the impact was lower than expected [39,40]. In 2014, we conducted a cross-sectional pilot survey in the province of Laguna (located on the Island of Luzon, in the Calabarzon Region of the Philippines). The survey was undertaken to confirm the appropriateness of the study site for the MGP trial by quantifying the prevalence of STH among ES children, particularly before the first implementation of the National School Deworming Day program on July 29, 2015 [41]. The results of the survey showed a prevalence of 33.3% by the Kato-Katz (KK) thick fecal smear microscopy technique for at least one type of STH infection [40]. Overall, the pilot survey indicated that Laguna satisfied the criteria as a study site to test the MGP and that STH continues to be a significant public health concern in the Philippines despite several years of MDA implementation.

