### Selection of Clusters/Schools

Sample size calculations were performed according to the study by Hayes and Bennett [46]. With an infection incidence of 18% and an intervention efficacy of 30%, the study had 80% power with a sample size of 20 intervention clusters (40 in total) and 38 students per cluster at the end of the trial, with a predicted annual 10% loss to follow-up.

Participating public ESs were selected using a spatial sampling technique to eliminate contamination between the intervention and control schools. From the list of schools that fit the criteria of 3 km radius distance from each other, 40 schools were randomly selected and assigned either to the intervention (MGP health education package) group or to the control group (no MGP health education package). Thus, 20 schools were randomly assigned to the intervention group, leaving the remaining 20 as controls. Figure 3 shows a map of the school locations.

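### Efficacy against infection is derived from an odds ratio although infection is common, so it overstates the risk reduction and can distort the comparison of endemicity strata

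*Protocol article*

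**What the plan says.** Under Study Outcomes, the protocol article makes infection one of two primary outcomes; knowledge is the other. Under Study End Point Analyses, infection is modelled by GEE, and "a logistic regression model will be used to estimate odds ratio and, therefore, intervention efficacy against infection", with allowance for clustering, repeated measures and baseline infection. The same paragraph adds that "Stratification by school-based baseline prevalence will be undertaken to evaluate intervention efficacy at low and high endemicity". It mentions no risk ratio, risk difference, log link or step from odds to risk.

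Two other sections bear on the scale. Selection of Clusters/Schools sizes the trial "With an infection incidence of 18% and an intervention efficacy of 30" per cent. Study Setting reports, for the trial province, "a prevalence of 33.3% by the Kato-Katz (KK) thick fecal smear microscopy technique for at least one type of STH infection".

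**The concern.** Readers of a prevention trial take efficacy to mean the share of infections prevented, 1-RR. The sample-size statement uses the word in a way that fits this: 30% efficacy on 18% incidence takes 18% to 12.6%. The analysis section takes efficacy from the odds ratio instead. The two scales agree closely only when the outcome is rare, and none of the article's prevalence or incidence figures is small enough for that.

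At stake are the efficacy figure on a primary outcome, intended for public health policy, and the stratified results. Strata formed by baseline prevalence differ in control risk by construction, so this is where the choice of scale matters most.

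**Working it through.** **Inputs.** From the article: design incidence p0 = 0.18, design efficacy 30%, 20 clusters per arm, 38 students per cluster at the end, 80% power (Selection of Clusters/Schools); pilot prevalence 0.333 (Study Setting). Assumed, because the article does not give them: two-sided alpha of 0.05, between-cluster coefficient of variation k, and a low-endemicity control risk of 10%.

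**Step 1: which scale fits the design figure.** The Hayes-Bennett formula for unmatched proportions is

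c = 1 + (1.96 + 0.84)² × [p0(1-p0)/n + p1(1-p1)/n + k²(p0² + p1²)] / (p0-p1)².

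- Efficacy as 1-RR: p1 = 0.7 × 0.18 = 0.126. With n = 38 and k = 0, the bracket is 0.1476/38 + 0.1101/38 = 0.00678 and (p0-p1)² = 0.002916, so c = 19.26, or 20 clusters, with 81.5% power. At k = 0.076, c is 20 and power is 80.0%.
- Efficacy as 1-OR: the odds are 0.7 × 0.18/0.82 = 0.1537, so p1 = 0.133. Power with 20 clusters is 68.9% at k = 0 and 67.1% at k = 0.076.

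Since k is not stated, the 80% cannot be reproduced from stated inputs alone. Under a two-sided test it fits the risk-ratio meaning with a small k, and it does not fit the odds-ratio meaning even at k = 0.

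**Step 2: the gap between the scales.** For control risk p and risk ratio RR,

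OR = RR(1-p) / (1 - RR·p), so (1-OR) - (1-RR) = RR·p(1-RR) / (1 - RR·p).

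This is positive for every RR below 1 and rises with p. At p = 0.18 and RR = 0.7 it is 0.0378/0.874 = 0.043. In the other direction, RR = OR / (1 - p + p·OR). At p = 0.18 and OR = 0.70 this is 0.70/0.946 = 0.740, a reduction of 26.0%.

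| Control risk | Source | True 30% reduction reads as 1-OR | OR of 0.70 is a true reduction of |
|---|---|---|---|
| 10% | assumed | 32.3% | 27.8% |
| 18% | design incidence | 34.3% | 26.0% |
| 33.3% | 2014 pilot | 39.1% | 22.2% |

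**Step 3: the strata.** With control risks of 10% and 33.3%, a constant 30% risk reduction would be reported as 32.3% and 39.1%, an apparent difference of 6.8 points. With a constant OR of 0.70, both strata would be reported as 30% although the risk reductions are 27.8% and 22.2%. The odds-ratio scale can therefore create a difference in relative risk reduction or mask one.

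These figures treat the odds ratio as unadjusted. Adjustment for baseline infection and covariates can move it further from 1; that effect is not quantified here.

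**The case against.** The strongest reply is that the article never writes efficacy = 1-OR. A logistic GEE can yield standardised risks, and a condensed article may leave that step to a fuller plan. This makes the 1-OR reading an inference. But the sentence names the odds ratio as the quantity from which efficacy follows and offers no other route, so the inference is the natural one.

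The size of the problem is also open to challenge. The only infection figure on which the trial was planned is 18%, where the overstatement is 4.3 points. The 33.3% comes from a 2014 pilot. It is not a control-arm risk at follow-up, and children in both arms are offered albendazole after baseline and again between the two follow-up surveys. That stands: 18% is the leading case and 33.3% a what-if.

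Three stronger readings are tempting, and the article does not support them:

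- *The stratified analysis will produce a false difference.* This needs the risk ratio to be constant across strata, and nothing in the article says that it is. No cut-off or stratum prevalence is given, and no formal between-stratum test is described.
- *The comparison with the earlier trial in China would be an artefact.* The article quotes a 50% efficacy for that trial but gives neither its definition nor the prevalence there, so this cannot be judged.
- *The sample size is wrong.* Step 1 shows that it is consistent with a risk-ratio efficacy and a small k. With k, alpha and sidedness unstated, the mismatch of scale between design and analysis is likely but not proven.

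Finally, logistic GEE is a standard, valid model for a clustered binary outcome, and the linear analyses of knowledge and behaviour scores are untouched. Both statements are right, and they limit the point to how the infection effect is expressed.

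**Conclusion.** The point holds as one of effect size and labelling, and should be fixed. If efficacy is computed as 1-OR, which is the natural reading, it overstates the proportional reduction in infection for any protective effect. At the design incidence of 18%, a true 30% is reported as about 34%, and a reported 30% is really about 26%. If control risk at follow-up reached the pilot's 33.3%, the figures would be about 39% and 22%.

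Efficacy compared between low- and high-endemicity schools on this scale can create or hide a difference in relative risk reduction. How large that would be depends on stratum risks that the article does not give; the 10% used above is an assumption. The validity of the test of no effect is not in question.

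**What to change.** Define efficacy against infection as 1-RR in Study End Point Analyses, so that it matches the natural meaning of the 30% in the sample size. Either of two routes will do:

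- a GEE with a log link (modified Poisson) and robust variance, keeping the planned clustering, repeated measures and baseline adjustment; or
- the planned logistic GEE, followed by marginal standardised risks in each arm and their ratio, with an interval that respects schools (delta method on the robust variance, or a bootstrap of schools).

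Report the risk difference alongside. The odds ratio can stay as a model result, labelled as an odds ratio and not as efficacy. Present the low- and high-endemicity results on the RR scale, with the control-arm risk in each stratum so that readers can see the absolute level.

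The cost is a sentence of analysis text and a different link or a short post-estimation step, with no new data. The efficacy figure becomes somewhat less favourable: about 4 points lower at 18% control risk if the true reduction is 30%. As the article says that analysis is under way, note the change and show both the odds ratio and the risk ratio, so that the choice of scale is visible.

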## Methods

### Study Design

Our overarching hypothesis is that a video-based health educational package (for use in schools) targeting STH will increase students’ knowledge of intestinal worms, their transmission, symptoms, treatment, and prevention and improve self-reported hygiene behavior. We addressed this hypothesis by conducting an unmatched cluster randomized intervention trial, targeting schoolchildren aged 9 to 10 years, in 40 schools in Laguna province, the Philippines. The trial study design is shown in Figure 1. The trial was conducted over the course of 1 year (June 2016 to July 2017). A total of 20 schools were randomly assigned to the *intervention* arm, in which the *MGP* health education package was delivered in combination with the standard health education activities (focused on WASH) endorsed by the Philippines Department of Health (DOH) and the Department of Education (DepEd). The other 20 schools comprised the *control* arm of the study, where the DOH/DepEd’s standard health education activities were implemented. At baseline, parasitological assessments and a STH-related knowledge, attitude, and practice (KAP) survey were carried out in all schools. In addition, height, weight, and hemoglobin levels were obtained from each consenting child; school attendance and academic performance were accessed from the school records. Only those children who had matched data on KAP and at least one stool sample at baseline were deemed eligible for assessments in the 2 follow-up surveys. The baseline (June-July 2016), first follow-up (Nov 2016-Jan 2017), and second follow-up (June-July 2017) surveys were completed using the same study measurements and quality-control assessments. The baseline survey was conducted immediately before the semiannual mass administration of albendazole in all schools, and follow-up surveys were conducted 5 months before the MDA [31].

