### Study Outcomes

The primary outcomes of the study are STH infections rates and knowledge of intestinal worms and their transmission, symptoms, treatment. Secondary outcomes are changes in self-reported behavior (hand washing, use of toilets, and food hygiene). Tertiary outcomes comprised measures of morbidity (hemoglobin levels to assess anemia; height and weight for stunted growth and malnutrition) and school academic performance and attendance for impact on education. All outcomes are compared between the control and intervention schools.

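### Knowledge, a primary outcome, is to be analysed as change with no baseline score named as covariate, unlike infection: valid as written, but less efficient than adjusting for baseline

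*Protocol article*

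**What the plan says.** Study Outcomes makes knowledge co-primary with infection: "The primary outcomes of the study are STH infections rates and knowledge of intestinal worms and their transmission, symptoms, treatment". Self-reported behaviour is secondary and is itself defined there as change.

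Study End Point Analyses treats the two primary outcomes differently within one paragraph:

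- **Infection:** a logistic GEE model, "accounting for clustering within schools, repeated measures, and baseline infection".
- **Knowledge and behaviour:** "Analyses of changes in knowledge and self-reported behavior scores will be analyzed with the use of a linear regression model and GEE", the purpose of the GEE being "to take into account clustering within schools and repeated measures". The baseline score is not mentioned.
- **Other covariates:** "Potential confounders such as age, sex, and rural or urban status of schools will be incorporated". This list is open and does not name the baseline score either.

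The baseline score exists. Study Design makes baseline data a condition for follow-up assessment: "Only those children who had matched data on KAP and at least one stool sample at baseline were deemed eligible". The section on the survey itself says: "All study participants were administered a questionnaire on STH-related KAP at baseline and at the 2 follow-up surveys".

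**The concern.** Subtracting the baseline score from the follow-up score fixes the baseline coefficient at 1. If the true slope of follow-up on baseline is below 1, as it is with equal SDs and any correlation short of perfect, two things follow.

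First, measurement noise in the baseline score enters the outcome, so the interval for a primary outcome, and for the behaviour outcomes, is wider than it need be.

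Second, if the arms happen to differ in baseline knowledge, the subtraction removes more than the part that persists to follow-up, and the remainder appears in the estimate with the opposite sign. Study Design describes the trial as unmatched, and the article describes no stratification of the 40 schools, so some chance imbalance in school-level knowledge is plausible.

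The covariate that would avoid both has already been collected.

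**Working it through.** **Inputs from the article.** Three surveys (baseline and two follow-ups); 40 schools, 20 per arm; 38 pupils per school at the end of the trial. The 80% power under Selection of Clusters/Schools is for infection only. No effect size, SD, intraclass correlation (ICC) or correlation over time is given for knowledge, so there is no stated figure to reproduce. All correlations below are assumptions.

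**Step 1: individual-level formula, one follow-up.** Let both scores have variance 1 and correlation ρ.

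- Change score: variance proportional to 1 + 1 − 2ρ = 2(1 − ρ).
- Baseline as covariate: variance proportional to 1 − ρ².
- Ratio, change to adjusted: 2(1 − ρ)/(1 − ρ²) = 2/(1 + ρ).

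| ρ (assumed) | 2(1 − ρ) | 1 − ρ² | Ratio | Power of change score if the adjusted analysis had 80% |
|---|---|---|---|---|
| 0.3 | 1.40 | 0.91 | 1.54 | 62% |
| 0.5 | 1.00 | 0.75 | 1.33 | 68% |
| 0.7 | 0.60 | 0.51 | 1.18 | 73% |
| 0.9 | 0.20 | 0.19 | 1.05 | 78% |

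The last column assumes two-sided alpha 0.05. It only illustrates scale, since the article states no power for knowledge.

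**Step 2: this design.** A simulation of 40 schools of 38 pupils, two follow-ups and 400 replicates per setting compared the change score with a model holding both the child's and the school-mean baseline score.

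| Child-level ρ | School-level ρ | ICC | Variance ratio, change to adjusted |
|---|---|---|---|
| 0.3 | 0.3 | 0.05 | 1.74 |
| 0.3 | 0.6 | 0.10 | 1.41 |
| 0.5 | 0.5 | 0.10 | 1.34 |
| 0.5 | 0.8 | 0.10 | 1.17 |
| 0.7 | 0.8 | 0.10 | 1.11 |

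The true effect was 0.3. Both estimators averaged between 0.297 and 0.305, so neither was biased. With 400 replicates the ratios carry some simulation error.

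**Step 3: why the top of this range exceeds 1.54.** Two follow-ups are pooled, which reduces follow-up noise but not baseline noise. Ignoring clustering, with the same ρ between any two surveys, the mean of two follow-ups has variance (1 + ρ)/2. The change from baseline then has variance (1 + ρ)/2 + 1 − 2ρ = 1.5(1 − ρ). The adjusted variance is (1 + ρ)/2 − ρ² = (1 − ρ)(1 + 2ρ)/2. The ratio is 3/(1 + 2ρ), which at ρ = 0.3 is 3/1.6 = 1.88.

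**Step 4: chance imbalance.** With equal SDs the baseline slope is ρ. If the arms differ by d at baseline, the expected follow-up difference is the effect plus ρd. Subtracting d leaves the effect minus (1 − ρ)d. At ρ = 0.5, half of the imbalance enters with reversed sign. In a clustered trial the slope that matters here is mainly the one between school means.

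**The case against.** Four arguments count against the point.

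1. **The wording may describe a longitudinal model.** Changes together with repeated measures could mean a model of the scores with baseline as one of three occasions. That reading is open. But if the baseline means of the arms are left free, the arm-by-time contrast is in essence a difference in mean changes, with essentially change-score precision. Only a model that constrains the baseline means to be equal would recover the loss, and the article does not say that.

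2. **The omission is read from silence in a condensed article.** A reader might infer that the plan has decided against baseline adjustment for knowledge. The text does not support that: the confounder list is open, and a fuller plan, not shown, may include the baseline score. What stands is that the article chooses change as the quantity analysed and names baseline for one primary outcome only.

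3. **Nothing is invalid.** A reader might infer that the knowledge result would be biased. It would not be: over randomisations both estimators are unbiased. The effect of imbalance in Step 4 is conditional on an imbalance having occurred.

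4. **The size cannot be fixed.** A reader might take a single percentage from the simple formula as the loss in this trial. The formula ignores clustering and the second follow-up, and every correlation is assumed. If knowledge scores are very stable, the loss is small.

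The second, third and fourth limit the point. None removes it.

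**Conclusion.** The point holds as one of efficiency and of handling chance imbalance, not of validity. As written, the analysis of a primary outcome and of the behaviour scores is sound but less precise than one that uses the baseline score.

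The change-score variance is about 5% higher at ρ = 0.9 and 54% higher at ρ = 0.3 by the individual-level formula, and 11% to 74% higher in the clustered simulation. These figures rest on equal SDs at each survey, on the assumed ICC of 0.05 to 0.10 and on the assumed child-level and school-level correlations. The simulated figures also rest on including the school-mean baseline score. The article supports a range only.

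A change is worth making because the baseline score is available for every eligible child and because the article already takes this approach for infection.

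**What to change.** State the knowledge and behaviour analysis as a linear GEE model of the follow-up scores at both surveys, with school as the cluster and with arm, survey and the child's baseline score as covariates, alongside the confounders already listed. The arm coefficient is the effect. Keep the change-score analysis as a sensitivity analysis.

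The school-mean baseline score is optional. The simulated gains include it, and it protects the gain if school averages persist over time much more strongly than individual children's scores. In that case the child's score alone would capture less of the benefit and could lose it.

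No new data are needed, but the change is not free. It uses one or two degrees of freedom with 40 schools. The article's Results section says that surveys are complete and analysis is under way, so the revised model should be documented before results by arm are seen. If they have been seen, it should be disclosed as a later change. If a fuller plan already adjusts for the baseline score, one sentence saying so settles the point.
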